# Medical Research Council Laboratories, Fajara. Application to undertake a research project.

**NB: This document is as submitted in 2002, although the budget has been removed, the consent form appended, and the exclusion of gametocyte carriers added (p9). This was decided prior to commencement of recruiting in 2002, and is explained in the manuscript. This exclusion was implicit in the original sample size calculation in this protocol (p8).**

**A4 Proposed start date and duration in months**

In giving a date please bear in mind the timescale for decision-making by SCC, the Ethical Committee and any other institutions whose agreement is needed, and the time needed to organise the resources required.

September 2002, for 3.5 months at Farafenni; data analysis to follow in London and The Gambia.

NB. This study follows those of 2000 and 2001 by the same investigators, in which we measured post-treatment transmission among children treated with several different antimalarial regimens.

**A5 Reference (office use)**

**Scientific Co-ordinating Committee No 910**

**Ethical Committee No 910**

**A6 Summary of project, long term objectives and specific aims (not more than 200 words)**

This section is very helpful to the Committees in determining quickly the main features of the study, and should be as clear and concise as possible. It should cover the key objectives and endpoints and, if the project is hypothesis driven, then the hypothesis should be stated here.

Widespread resistance of *Plasmodium falciparum* to commonly-used drugs has lead to the formulation and testing of new combinations of anti-malarials, particularly those including one of the artemisinins. This proposal is one in a series of trials with the long-term objective of identifying highly efficacious drug combinations that also reduce or prevent post-treatment transmission of *P. falciparum*. Our studies in 1998-2001 have shown that:

- Sulphadoxine/pyrimethamine (SP; Fansidar®) treatment is followed by high gametocytaemia in a large proportion of subjects.
- Compared to SP, artesunate (AS) + SP reduces, but does not prevent, transmission of *P. falciparum* to mosquitoes (9).
- the prevalence of resistance to chloroquine (CQ) is sufficiently high in the Farafenni area to severely compromise CQ + AS as a treatment for uncomplicated malaria.
- CQ + AS reduces transmission at day 7, but this benefit is probably transient, as gametocyte carriage increases significantly in the latter half of follow-up, and these gametocytes are likely to have CQ-resistant genotypes.

Thus whereas both of the AS combinations we have tested do reduce the infectiousness of treated children, neither can completely prevent transmission. The CQ + AS combination has the added disadvantage of poor efficacy, whereas SP + AS is efficacious but permissive of post-treatment transmission. The results of this series of trials rank SP + AS as the best combination tested to date, suggesting that the anti-folate class of drugs make good partners for AS. The chief disadvantages of this regimen are that transmission can occur in 5 to 10 % of infected children treated with this combination, and that SP has proved to be very vulnerable to rapidly progressing drug resistance in other African settings. This is partially due to its very long half-life in the patient’s circulation (2). It follows that any parasite remnant that survives AS (a drug that is rapidly cleared) will be under a lengthy period of selection by SP. The prevalence of resistance to SP is low around Farafenni, but greater than zero (11) so that widespread administration of this combination may lead to the emergence of SP resistance as a serious threat to long-term efficacy.

We have not met our chief aim of identifying antimalarial combinations that are safe, affordable, highly efficacious and which reduce or completely ablate post-treatment transmission when used to treat Gambian children with uncomplicated falciparum malaria. A new candidate for transmission-reducing treatment is required. We propose to test the infectiousness of children treated with artemether + benflumatol (Co-Artemether), as clinical trials in The Gambia have shown this drug to be highly efficacious, and suggest that post-treatment gametocyte-carriage is low (12, 13). Gametocyte prevalence and density, and the infectiousness to mosquitoes of treated persons have not been systematically measured for Co-Artemether.

A7 Checklist/Signatures

**Please complete the following checklist and comment as appropriate.** This section is designed to ensure that all the planning steps have been taken that are needed for successful project. For projects at the MRC Laboratories, Programme Heads will help visiting workers, and others preparing proposals at a distance, to ensure liaison with key individuals who need to be consulted locally.

1. **Has the project been discussed and cleared with the institutions in which research will be carried out including health services to which the study will need access?**

Yes

1. **Have all investigators and collaborators given their agreement to take part in the study as described?**

Yes

1. **Has a CV been attached for the principal investigator if unknown to the Committee?**

Not applicable

1. **Have ethical issues been addressed? Give details in section C.**

Yes

1. **Have safety issues been addressed? Please give details**

Yes

1. **Will the project require data and/or materials to be taken out of The Gambia? If so please give details** Data will be analysed at LSHTM in collaboration with MRC staff in The Gambia. We plan to take the following material out of The Gambia to either LSHTM or the University of Edinburgh (*):

- filter-paper blood spots for parasite genotyping studies
- small (~50l) blood samples for parasite RNA extraction *
- alcohol-fixed oocysts from mosquito guts *
- frozen sera used in transmission experiments
- paraformaldehyde-fixed parasites on microscope slides for immunofluoresence*

1. **For projects to be carried out at MRC Laboratories: Have the following been consulted about the support services, resources and working space required?**

|  | **Consulted: Yes/No/Comment** |
| --- | --- |
| Laboratory Manager (including safety issues) | Ongoing |
| Director of Clinical Services | Project at AFPRC hospital/MCH clinic, discussed with CE hospital, and DHT |
| Head of Computing | Data-entry at Farafenni field station, overseen by [name] |
| Transport Manager | Ongoing |
| Finance Manager | Ongoing |
| Personnel Manager | Ongoing |
| Administrative Director | Ongoing |
| Other services – specify | Modest requirement for printing forms to be done at Farafenni |

**Signature of principal investigator: Date:**

**__________________________________________________________________________**

**B Description of Project**

**B1 Background**

In response to the widespread occurrence of CQ-resistant parasites in Africa, and the more recent demonstrations that resistance to sulphadoxine/pyrimethamine (SP) is reducing the efficacy of that drug (1, 2,5), calls have been made for the deployment of new effective antimalarial combinations. Of particular interest are the artemisinins, which have short elimination half-lives, in various combinations with longer-acting drugs (11-14). Recent trials of AS in combination with SP in Africa have shown this to be a safe and efficacious regimen (9,11), but that a certain level of post-treatment transmission occurs (9). It is of importance to determine the effects of the artemisinins on *P. falciparum* transmission, and to use this information in the formulation of appropriate combination therapies for use in Africa.

We have run a series of trials in which we can measure *P. falciparum* gametocyte prevalence, density and infectivity to mosquitoes after treatment with artemisinins in various combinations with other anti-malarials. This work has been carried out at the MRC field station at Farafenni, The Gambia, during four consecutive malaria transmission seasons (1998 and 1999; ref. 7; 2000 and 2001, [name] et al., unpublished). In total 2,136 children have been treated with either CQ alone, CQ plus AS, SP alone, SP plus AS or SP plus CQ.

## Our studies in 1998/9 showed that AS, in combination with SP, reduced both the mean density of gametocytes in positive subjects, and the prevalence of gametocytes in the treated population (9) compared to SP alone. Nevertheless, a gametocyte prevalence of 5-10% was observed at day 7 in the combination group, and these gametocytes were capable of infecting mosquitoes in membrane-feeding experiments (9). Therefore, there may still be considerable transmission after treatment with AS combined with SP.

In 2000, we compared treatment with the combination CQ plus AS (3 days) with CQ alone. The results of this trial are now being prepared for publication, and can be summarised thus:

- CQ monotherapy exhibited a clinical failure rate of 13.3% and a cumulative parasitological failure rate of 75.6% over 28 days.
- The combination CQ/AS exhibited a clinical failure rate of 8.5% and a cumulative parasitological failure rate of 52.1% over 28 days.
- There was no significant difference between the two regimens in the total proportion of clinical failures over 28 days. The addition of AS to CQ prevented clinical failures occurring within 14 days of treatment, but provided no benefit in the latter half of follow-up.
- Gametocyte carriage was significantly reduced in the combination group up to day 14, but day 28 gametocyte carriage rates were high in both groups: 34% for CQ and 21% for CQ +AS.
- Children identified as gametocyte carriers on day 7, but who were gametocyte-negative on admission, were tested for infectiousness to *Anopheles*. Gametocyte-carriers from both groups were infectious, although gametocytes from children receiving CQ plus AS were less infective on average (Drakeley, [name] and [name], in preparation).

We conclude from this study that addition of AS to CQ does transiently reduce clinical failures and transmission immediately post-treatment. However, the cumulative parasitological failure rate of over 50%, and the high gametocyte carriage observed in the second fortnight of follow-up preclude this combination from any future role as first-line therapy in The Gambia.

Although none of the combinations so far tested are ideal for both transmission reduction and delivery of adequate clinical and parasitological efficacy, the best results have been obtained with SP / AS. Thus artemisinin combinations still hold the most promise in terms of both efficacy and public health benefit.

We propose a randomised controlled trial to compare the effect of Co-Artemether on post-treatment transmission. This will be compared to the effect of CQ combined with SP. CQ / SP provides a reference treatment group for comparison to our previous studies, as well as conforming to current Gambian Government guidelines for second-line treatment of uncomplicated malaria.

### B2 Project description

Project aim:

- Using a randomised control trial (RCT) design, measure the transmission potential of Gambian children after treatment with anti-malarial drugs.

Study aim for 2002:

- Measure *P.falciparum* transmission after Co-Artemether vs CQ plus SP by comparing gametocyte carriage rates and infectiousness to mosquitoes.

Secondary aims:

- To measure the prevalence of alleles associated with CQ drug resistance among pre-treatment isolates, parasitological treatment failures, emergent gametocytes and mosquitoes infected by membrane-feeding.

**Specific objectives:**

1. Using gametocyte prevalence, density and infectivity to mosquitoes by membrane-feeding as outcome measures, we plan to test whether Co-Artemether effectively reduces transmission compared to CQ / SP and, by reference to our previous work, compared to other antimalarial regimens.
2. Use PCR genotyping at loci implicated in CQ drug-resistance (8) and other polymorphic loci, in combination with data on treatment failures, to estimate the prevalence of resistant parasites in pre-treatment infections, in the emerging gametocyte population, and among treatment failures. Oocysts from infected mosquitoes will also be typed to look for evidence of drug selection in transmission. The relative contribution of resistant genotypes to circulating gametocyte pools will be estimated using the *in situ* PCR approach with our collaborators [name], [name] and [name] (3,4).
3. Use RT-PCR amplification of RNA from infected peripheral blood to establish stage specificity of parasite samples as recently described (7), and to examine genetic complexity of gametocyte populations *in vivo* by PCR analysis of polymorphic loci.

**Experimental Design and Methods to be Used**

###### Clinical trial and transmission experiments

Over the four previous seasons, we have established a randomised controlled trial (RCT) protocol, modified from the standard WHO guidelines for efficacy trials, for the examination of post-treatment transmission of falciparum malaria. In these trials based at the Farafenni Health Centre we recruited 600 children over 15 weeks, 500 children over 10 weeks, 536 children over 9 weeks and 500 children over 10 weeks respectively. These rates of subject recruitment, combined with accumulated gametocyte prevalence data will be fed into the design of the new protocol.

Children aged 1-10 years attending the Farafenni APRC Hospital or MCH clinic and requiring treatment for uncomplicated malaria will be recruited into the study after appropriate consent has been obtained from a parent or guardian. They will be randomly assigned to a treatment group by clinicians of the MRC Station, Farafenni, in a ratio that reflects *a priori* estimates of gametocyte carriage rates in the different treatment groups. Clinical and demographic data will be recorded on a standardised case report form (CRF) as in previous years. The principal investigator, slide readers and entomologists will be blinded as to the treatment group of each child. Field workers will be required to monitor drug doses on days 2 and 3 in the child’s home and therefore cannot be blinded. Blood films, blood spots and a microtainer blood sample will be obtained at the time of treatment. The blood sample will be used to measure PCV, genotyping parasites and previous antimalarial use.

On follow-up day 7, the child and a guardian will be brought to the field station for gametocyte-screening clinic, where duplicate thick films and filter-paper blood-spots will again be collected. Temperature and PCV will be measured and the mother and child questioned concerning any continuing clinical malaria symptoms. Each child will be asked to remain at the field station until one thick film has been read. If gametocytes are present, and permission given, approximately 3 ml of blood will be taken by venous puncture and immediately processed for mosquito infection studies.

All subjects will also be actively followed up at home on days 14 and 28 post-recruitment. On both occasions, 2 thick films will be taken, and blood spotted onto filter paper for genotyping. Parents and guardians will be encouraged to bring the child back to the clinic at any other time the child is unwell.

Farafenni MRC has two purpose-built insectaries. Previously, we have bred F1 generation *Anopheles gambiae* from wild caught mosquitoes for these experiments but [name] and colleagues have recently successfully established a stable colony of *A. gambiae* in the Farafenni insectaries which we will use as the source of adult mosquitoes for membrane-feeding in the coming season.

We will analyse the results of the trial for relevant clinical, parasitological and entomological parameters, with particular emphasis on transmission endpoints. Previously, we have used two summary statistics (the probability of post-treatment infectiousness, and the infectious proportion of subjects) that incorporate gametocyte prevalence, density and infectivity to mosquitoes (9). These data will then be related to the estimated proportion of treated infections in rural areas of The Gambia to derive an estimate of the contribution that children treated with each regimen would make to transmission.

###### Parasite genotyping

Along with our collaborators at Edinburgh University, we are now establishing the necessary capacity to perform basic molecular biology in the MRC laboratories at Farafenni. The two collaborating groups have provided a PCR machine and electrophoresis equipment from the Gates Malaria Programme at LSHTM, and the MRC project funding held by [name] and [name] in Edinburgh. Our collaborators’ MRC funding is also supporting a higher scientific officer with experience in molecular biology ([name] [name]), and our Gates Malaria Partnership funding will allow us to provide any further training he requires in the specific area of drug-resistance genotyping which is to be used in these and other studies.

A novel application of RT-PCR has allowed us to detect expression of developmental stage-specific genes in peripheral blood obtained at the time of feeding mosquitoes (7). RT-PCR of an asexual-specific locus (*resa*) and a gametocyte-specific locus (*pfs16*) permits samples with gametocytes only and samples with sub-patent asexual parasites as well to be distinguished from each other. Thus we can clarify whether the DNA in our genotyping experiments is derived just from gametocytes, or from a combination of gametocytes and asexual parasites, within the limits of detection of our RT-PCR system. The results of this molecular genetics approach have clearly demonstrated that day 4 and day 7 circulating gametocytes comprise a mix of, on average, two or more genotypes. Thus in our study area the requirements are being met for heterologous genetic recombination to occur in the mosquito. This is the first time such an analysis has been reported. However, this work included only 10% of our study subjects, and a meaningful comparison among treatment groups was not possible with this sample size. We plan an expansion of this work to other drug treatment groups, and with larger sample sizes, using these methodologies.

**B3 Details of study design and investigations**

1. **What type of study design is proposed (eg case control, prospective cohort, randomised controlled trial, descriptive etc)**

Randomised Controlled Trial

1. **What is the proposed size of the study (this may relate to patients, cases, controls, survey subjects, laboratory samples etc, as appropriate).**

The aim is to recruit approximately 550 patients over 11 weeks.

1. **Please describe the statistical considerations and sample size calculations involved in determining the size of the study.** (If you do not have access to statistical advice, please consult the MRC Laboratories Statistics Department.)

Approximately 550 patients will be treated.

In our previous studies the lowest observed gametocyte rate 7 days after treatment was ~8% (excluding those who had gametocytes on day 0), seen after treatment with CQ + artesunate. We expect that the rate after Co-Artemether will also be 5-10%. Gametocyte rates after CQ / SP treatment are much higher, between 40% and 50% at day 7. We will aim to enrol 450 subjects in the Co-Artemether group, and 100 subjects in the group receiving CQ / SP. All treated children will be screened for gametocytes on day 7 only. We expect to be able to perform 20 to 40 membrane feeds and 40 to 50 membrane feeds respectively in the Co-Artemether and CQ / SP treatment groups. This will provide a power of 80% at the 95% confidence level to detect a 9-fold difference in average probability of mosquito infection (as observed between SP / AS and SP in 1999). We will have a power of 80% at the 90% confidence level to detect a five-fold difference in the proportion of infectious children in the two groups (as observed in 1999).

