##### Exclusion Criteria

Signs or symptoms of severe malaria including severe anaemia (PCV <20% or Hb<5g/dL), hyperparasitaemia (>500 parasites per hpf, ie 250000 per ul) or convulsions.

**Children displaying any of the above signs will be directly admitted to the paediatric ward of the APRC Hospital** **by the recruiting physician (SD, GW).**

Vomiting or inability to take drugs orally. **Alternative treatment will be administered.**

A history of anti-malarial treatment in the past two weeks.

Evidence of any other chronic or acute illness.

Infection or co-infection with non-falciparum malaria parasites.

Patent gametocytaemia.

1. **How will informed consent be obtained?**

Informed consent will be obtained from a parent or guardian at the time of enrolment into the study (Consent form attached). The aims and methods, including details of blood samples needed, will be explained in a language they understand. The recruiting field worker/nurse will sign that consent was given. The right of all individuals not to participate or to withdraw their consent will be respected and the children will then receive standard treatment. Parents may withdraw their consent at any point in the trial and the child’s treatment will not be affected.

1. **What samples, if any, will be taken and what investigations will be conducted?**

- Finger-prick blood samples on days 0, 7, 14 and 28 to provide thick films for parasite detection and filter paper blood spots for molecular typing of parasites.
- Microtainer samples on day 0 for PCV, genotyping and RT-PCR
- 2-3ml blood by venepuncture on day 7 from consenting gametocyte-positive patients for membrane feeding of mosquitoes.
- Alcohol-fixed oocysts from infected mosquito guts for genotyping

1. **Will treatment be given? YES**

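### The sample-size section limits gametocyte screening to day 7, which conflicts with outcomes that have no day limit and leaves it unstated whether the day 14 and 28 films are read for gametocytes

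*Protocol*

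**What the plan says.** - **Screening rule (B3, sample-size answer):** "All treated children will be screened for gametocytes on day 7 only". The sentence stands between the arm sizes (450 and 100) and the expected numbers of membrane feeds.
- **Outcomes (B2, Specific objectives):** "Using gametocyte prevalence, density and infectivity to mosquitoes by membrane-feeding as outcome measures". No day is attached. The 2002 study aim likewise compares carriage rates and infectiousness without naming a day.
- **Day 7 (B2, Clinical trial and transmission experiments):** children attend a screening clinic, and one film is read while they wait. "If gametocytes are present, and permission given, approximately 3 ml of blood will be taken by venous puncture".
- **Later visits (same section):** "All subjects will also be actively followed up at home on days 14 and 28 post-recruitment". Each of these two visits includes duplicate films and a filter-paper sample, with no mention of gametocytes.
- **Purpose of the films (B3, answer on samples, printed under Exclusion Criteria):** "Finger-prick blood samples on days 0, 7, 14 and 28 to provide thick films for parasite detection".
- **Earlier evidence on CQ + AS:** the A6 summary says of its day-7 effect that "this benefit is probably transient, as gametocyte carriage increases significantly in the latter half of follow-up". B1 reports a significant reduction in carriage up to day 14, and then "day 28 gametocyte carriage rates were high in both groups: 34% for CQ and 21% for CQ +AS".

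**The concern.** The trial is about transmission after treatment, and gametocyte carriage and density are two of its three outcome measures. The only sentence that fixes when gametocytes are looked for confines this to one day. A slide reader who followed it would not record gametocytes on the day 14 and 28 films. A later analysis plan could not use counts that were never made.

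The team's own history makes this more than a matter of tidiness. For CQ + AS, day 7 gave an incomplete picture: carriage rose later, and high carriage in the second fortnight was one of two reasons given in B1 for ruling the combination out. The B3 sample-size answer then uses the day-7 rate of that same regimen, about 8%, in setting the 5-10% expected for Co-Artemether. B2 also plans to estimate how much children treated with each regimen would contribute to transmission. If prevalence and density come from day 7 alone, that estimate rests on one day.

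**Working it through.** **1. The plan's own figures around the sentence.** Expected feeds = children × expected day-7 carriage.
- Co-Artemether: 450 × 0.05 = 22.5 and 450 × 0.10 = 45 (stated 20 to 40, about 89% of these).
- CQ / SP: 100 × 0.40 = 40 and 100 × 0.50 = 50 (stated 40 to 50).

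The feed counts therefore follow from day-7 carriage, which fits a reading of the sentence as being about selection for feeding. The two stated power figures (80% for a nine-fold and for a five-fold difference) concern infection of mosquitoes and infectious children. Neither concerns carriage. The five-fold figure can be neither confirmed nor refuted, because no baseline is given. With all treated children as denominator and a two-sided 10% level it would need about 5.7% against 1.1% infectious. The present point does not depend on it.

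**2. The passages side by side.**

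| Item | Day 7 | Days 14 and 28 |
| --- | --- | --- |
| Outcomes in B2 | carriage, prevalence, density, infectivity | no day limit stated |
| Thick films | duplicate | two per visit |
| Gametocyte reading stated | yes (B2, B3) | nowhere; B3 says day 7 only |
| Blood for feeding | yes | none |

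The literal rule and the undated outcomes cannot both be followed at days 14 and 28. Infectivity is confined to day 7 on any reading, because feeding blood is taken only then.

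**3. Would reading the later films be informative?** Assumption: day-28 rates as in the 2000 trial, 34% in the 100 CQ / SP children and 21% in the 450 Co-Artemether children. Those rates belong to CQ and CQ + AS, so this is only an illustration.
- Pooled rate: (34 + 94.5) / 550 = 0.2336.
- Null SE: √[0.2336 × 0.7664 × (1/100 + 1/450)] = 0.0468.
- Alternative SE: √[0.34 × 0.66/100 + 0.21 × 0.79/450] = 0.0511.
- z = (0.13 − 1.96 × 0.0468) / 0.0511 = 0.75, so power is about 77% at two-sided 0.05 (85% at 0.10).
- With an assumed 10% or 20% loss in each arm, power at 0.05 is 73% or 68%.
- With 34% in the control arm, 80% power needs about 20.5% or less in the Co-Artemether arm.
- A 21% rate in 450 children has a 95% CI half-width of 1.96 × √(0.21 × 0.79/450) = 3.8 points.

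For comparison, day-7 carriage at the planned rates (40-50% against 5-10%) has power above 99.9%. The later comparison is weaker but usable.

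**4. Workload.** 550 children × 2 visits × 2 films = 2,200 films, all already scheduled.

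**The case against.** The best defence is that the sentence describes selection for membrane feeding. It sits directly before the feed counts, and B2 uses the word screening for the day-7 clinic where a positive film leads to venous blood. B2 (Parasite genotyping) also mentions earlier work on day-4 and day-7 gametocytes, so the word only may mean that no day-4 screening is planned; that is an inference. Parasite detection, as the purpose of the films, covers all four days. It must include gametocytes on day 0, where patent gametocytaemia is an exclusion, and on day 7. The design continues a series in which the 2000 trial did report day-28 carriage. Detailed by-visit analyses can also be left to an analysis plan, which is not shown.

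Much of this stands. The feeding reading is plausible, and the description of the films does not exclude gametocytes. It does not remove the conflict, because the protocol never states that reading and never says that the later films are read for gametocytes.

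A reader might go further and infer four things that the documents do not support:
- **That the trial cannot detect a late rise.** The day 14 and 28 films are collected, so the information exists if they are read.
- **That late data overturned the day-7 result for CQ + AS.** The benefit was significant up to day 14, day-28 carriage was still numerically lower than with CQ (21% against 34%), and the team wrote only that the benefit was probably transient. The rejection also rested on cumulative parasitological failure above 50%.
- **That carriage rebounded by day 14.** B1 says the reverse.
- **That about 95 Co-Artemether carriers would be missed at day 28, against 36 on day 7** (450 × 0.21 = 94.5; 450 × 0.08 = 36). This carries CQ + AS rates over to a drug that A6 describes as highly efficacious with carriage suggested to be low. The 8% also excludes day-0 carriers, and the 21% may not.

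**Conclusion.** The point holds as a conflict in wording on a central outcome. It is not a demonstrated inability of the design. Taken literally, the B3 sentence drops gametocyte reading from films that the protocol already collects, against outcomes that carry no day limit. On the milder reading the sentence says something other than was meant, and nothing elsewhere corrects it. Both readings call for the same edit.

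What is at stake is whether the carriage comparison covers one day or the 28-day follow-up. No figure for missed carriers can be taken from the documents for Co-Artemether. The 77% power for a day-28 comparison assumes the 2000 rates and complete follow-up, and shows only that reading the films would be worthwhile. Reading them would recover carriage and density. It would not recover infectiousness after day 7. The correction is worthwhile and cheap, but the evidence does not make it a condition for the trial to proceed.

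**What to change.** Replace the B3 sentence with wording such as:

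> Children are screened on day 7 to select those for membrane feeding. Thick films of days 7, 14 and 28 are read blinded for gametocytes, and carriage and density are compared between arms by visit.

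Add that infectivity results apply to day 7 only, and carry the same limit into the planned estimate of each regimen's contribution to transmission. Slide readers are already to be blinded under B2, so no new blinding arrangement is needed.

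The cost is gametocyte counts on up to 2,200 films already scheduled for days 14 and 28. There are no new visits, blood samples or feeds.
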